### Data collection

#### Quantitative data

Effectiveness outcomes will originate from the data sources shown in table 2. Data collected by nurses or data operators from the EHR include age, gender, duration of diabetes, use of insulin, parental history of diabetes, other complications of diabetes including diabetic kidney disease, cardiovascular complications, and diabetic foot, random blood sugar results, urine dipstick test for albuminuria and blood pressure record. Other study-specific data collected by nurses or data operators on the day of screening include education status, occupation and income categories, and previous history of DR, cataract surgery or any other ocular history. In addition, they will measure body mass index, waist circumference and complete a lifestyle questionnaire on smoking, diet, physical activity, EQ-5D vision bolt-on.^24^ The EQ-5D vision bolt-on will be used to calculate the quality adjusted life-years and utility value for economic analysis. EQ-5D alone does not capture visual acuity deficits.^25^ The EQ-5D vision bolt-on asks patients to rate their health across six dimensions: mobility, self-care, usual activities, pain/discomfort, anxiety/depression and vision. Each dimension is scored in five levels: no problems, slight problems, moderate problems, severe problems and extreme problems. A recent study provided utility values based on EQ-5D vision bolt-on. The mapping was done in a clinical trial cohort with macular oedema in central retinal vein occlusion.^26^

In the reading centre, the data collection will include the grade of retinopathy in both eyes, presence of cataract and gradability of the retinal images. Data collected on referred patients will include numbers with ungradable images due to cataract, treatment options offered for DR and review appointment.

#### Qualitative data collection and analysis

Data sources used for evaluation of the implementation strategy are shown in table 3. These will include data from a structured interview of a maximum variable sample that will reflect the context (primary, secondary and tertiary care), and the functions and skill levels of the staff (eg, nurses, doctors, etc.). Based on pragmatic considerations, at least five nurses and five primary care doctors from 16 FHCs, three to five ophthalmologists from secondary and tertiary care, two data entry operators and five ASHAs and one health service administrator should be included to get the maximum variability. Verbal consent will be obtained from these health professionals. The interviews will be conducted by an independent member from the GCRF/UKRI-funded team, who is not involved in this study, in the local language within the premises of the healthcare provider. The focus group will consist of groups of patients and staff within one FHCs. In addition, to the voice-recording of the interviews and focus group, interviewers will write field notes to describe the interview situation. The interviews and focus group content will provide the basis for the data analysis, which will be based on a descriptive phenomenological approach without data or opinion interpretation and will include transcription, condensation, coding and categorisation using qualitative analysis tools. We will use the field notes collected during the interviews to inform the understanding of the phenomenon studied.

A survey of all referred patients will be done using a structured questionnaire to evaluate their satisfaction and their perception of the barriers and facilitators. All qualitative data will be coded using NVivo and analysed using descriptive phenomenological approach following the strategy.^27^ We will transcribe the interview data, identify statements or phrases, create formulated meanings or meaning units, aggregate formulated meanings and incorporate the result into descriptions.

### Data monitoring

Data will be coded before entry into the study database by the clinical teams. Only anonymised extracted data from EHR by the nurses or data entry operators will be used for analysis. Data quality will be monitored by the study project manager. Anonymised data will be checked for range checks and data quality at University of East London by the study statistics team. The ORNATE India International Advisory Board will have an overview of the conduct of the project and the Executive Group consisting of the UK-India collaborators will monitor the conduct of the study.

### Sample size

We have chosen the proportion of patients in the non-communicable diseases register with diabetes screened for DR as our primary outcome variable.

Justification of the choice of primary outcome: this variable captures the effectiveness of our intervention as well as the fidelity of implementation. Other facts that informed our choice of the primary outcome is that we expect a short implementation time of 7–9 months during which other outcomes such as number of patients treated may not be a feasible option. Therefore, we have estimated the sample size based on this primary outcome.

Our calculations are complicated by the expected increase in number of people with diabetes in the non-communicable diseases register as public awareness of diabetes and DR increases so the denominator of numbers screened will be the number of people registered in the non-communicable diseases in each FHCs at the start of the cross-sectional study. There is no data on the baseline proportion of patients that attend the tertiary centre for screening. The prevalence of diabetes is between 10% and 16% in Thiruvananthapuram of which 8% are estimated to have DR and 3% to have STDR but about 20% may have to be referred. Assuming a finite population of 40 000 patients with diabetes, a simple random sample of 377 patients will be needed. However, we expect large design effects due to clustering patients within FHCs. There is not enough data to calculate the value of this design effect and therefore we assume it to be 3 to give a final sample size of 1131, which is equivalent to assuming a within-FHCs intracluster correlation coefficient of approximately 0.03 (n=16 FHCs) with negligible residual clustering by the intermediate cluster level of ASHAs, where mean cluster size is smaller.

As described by Becker *et al* in mammography screening,^28^ we expect sources of bias in the implementation programme that will likely influence the sample size calculation. Unscreened DR cases that already exist in the community may contribute to an over-estimation of the effect of screening. We expect lead-time bias because of our short implementation period and so some DR in the community may be missed. A comparison of numbers with DR in FHCs with longer implementation period with those of shorter period may adjust for this bias. We intend to provide a descriptive analysis as well as a temporal comparison using time series analysis.

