## Methods

### Design

We chose a type 2 hybrid effectiveness-implementation design to evaluate the effectiveness of the clinical interventions and the implementation strategies.^20–23^ Mixed methods will be used as the method of evaluation. DR care pathway was developed by the Kerala Health Secretary, non-communicable diseases lead, Health and Medical Education service providers, technical and EHR teams, local authorities and the GCRF/UKRI-funded coapplicants from the UK. The DR care pathway will be set-up in a staggered approach with five FHCs initiated in the first 3 months and the remaining 11 centres will be added based on acceptance of all stakeholders and adapting and training phase for 12 months from 15 March 2018. A further 12–15 months will be allocated to recruit consenting patients to a cross-sectional study to gather quantitative data for the effectiveness outcomes. A minimal data set from this study will also be entered into EHR to enable future screening for the consented patients. Qualitative data collection from interviews of staff, patients and focus groups at baseline and end of study and all field notes gathered during the study will be utilised to inform evaluation of the implementation strategy.^20–22^

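### Cases missed in a short screening period are labelled lead-time bias, and comparing case counts between longer- and shorter-running centres cannot adjust for either problem

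*Protocol article*

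**What the plan says.** The Sample size section of the protocol article names the bias and its cause: "We expect lead-time bias because of our short implementation period and so some DR in the community may be missed". The next sentence gives the remedy: "A comparison of numbers with DR in FHCs with longer implementation period with those of shorter period may adjust for this bias". It states no denominator, rate or allowance for time at risk.

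Three timing statements bear on it:
- Sample size: "we expect a short implementation time of 7–9 months".
- Design, on the staggered start: "five FHCs initiated in the first 3 months and the remaining 11 centres will be added based on acceptance of all stakeholders".
- Design, on recruitment: "A further 12–15 months will be allocated to recruit consenting patients to a cross-sectional study".

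Other parts of the article do use denominators or handle time. Description of the standard of care bases prevalence on the people screened. Statistical analyses adds each FHC's month of entry as a covariate. The Sample size section closes with an intention to give descriptive results and a time-series comparison. None of these is tied to the bias comparison.

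**The concern.** There are two separate problems.

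**The label.** Lead-time bias is an apparent benefit produced by moving the date of diagnosis forward. Measuring or removing it requires follow-up from diagnosis to a later outcome. The quantitative component described is one cross-sectional round. What the article describes, cases not found because screening ran briefly, is incomplete coverage.

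**The remedy.** A count of people found with DR is the product of prevalence, screening rate and screening time, limited by the size of the register. A longer-running FHC can therefore show more cases with no bias present. Start dates are also not assigned at random: the later FHCs join when stakeholders accept. Longer-running FHCs may thus differ in readiness as well as in duration.

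At stake is the reading of DR and STDR yield. A difference produced by screening time could be reported as evidence about bias, or the text could suggest a protection that the analysis does not provide.

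**Working it through.** **Inputs**
- Sample size section, prevalence among people with diabetes: 8% for DR and 3% for STDR.
- Sample size section, population and simple random sample: "Assuming a finite population of 40 000 patients with diabetes, a simple random sample of 377 patients will be needed".
- Sample size section, on the inflation for clustering by design effect: "we assume it to be 3 to give a final sample size of 1131".
- 16 FHCs, 5 started early and 11 later (Design).
- Assumed here: the 5 early FHCs are the longer-running ones, DR prevalence is 8% everywhere, and every FHC screens the same number per month.

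**The plan's own figures.** The article gives no figure for the bias comparison, so only the sample size can be reproduced. With an assumed margin of ±5 points, 95% confidence and a proportion of 0.5, n0 = 1.96² × 0.25 / 0.05² = 384.1. The finite-population correction n0 / (1 + (n0 − 1)/N) gives 380.5 for N = 40 000, within 3% of 377. Then 377 × 3 = 1131, and the intracluster correlation is (3 − 1) / (1131/16 − 1) = 0.029, against a stated value of about 0.03.

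**Expected counts with no bias.** Monthly rate per FHC: r = 1131 / (5 × long months + 11 × short months). Expected DR cases per FHC = 0.08 × r × months.

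| Months, long v short | r | Screened per FHC | DR cases per FHC | Count ratio | DR among screened |
|---|---|---|---|---|---|
| 9 v 7 | 1131/122 = 9.27 | 83.4 v 64.9 | 6.67 v 5.19 | 1.29 | 8% v 8% |
| 15 v 12 | 5.46 | 82.0 v 65.6 | 6.56 v 5.25 | 1.25 | 8% v 8% |
| 12 v 3 (assumed extreme) | 1131/93 = 12.16 | 145.9 v 36.5 | 11.67 v 2.92 | 4.0 | 8% v 8% |
| 12 v 12 (common window) | 5.89 | 70.7 v 70.7 | 5.66 v 5.66 | 1.0 | 8% v 8% |

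The count ratio is simply the ratio of months. The proportion with DR among those screened does not move.

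**Saturating register.** Take 40 000/16 = 2500 registered people per FHC and a constant monthly uptake hazard h. The number screened by month t is 2500 × (1 − exp(−h t)). For 9 v 7 months the count ratio falls from 1.28 (h = 0.004) to 1.06 (h = 0.3). For 12 v 3 months it falls from 3.93 to 1.64. The hazards are assumptions chosen to show the range.

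**False signals with no bias.** Data were simulated at 8% prevalence in every FHC, ignoring clustering, with 5% two-sided tests. At 9 v 7 months, a test of counts per FHC rejects in 20% of trials with 1131 screened and in 93% with an assumed 10 000 screened. A test of the proportion with DR among those screened rejects in about 5% in both cases.

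**The case against.** The strongest reply is that the article says only that the comparison may adjust. It is one tentative sentence with no estimator, and the Statistical analyses section contains no such step. The article also uses the word numbers loosely, and its reported prevalence has a denominator, so a rate may be what is meant. On the article's own description of the bias, more cases in longer-running FHCs is the expected sign of incomplete coverage.

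Much of this stands. A reader might infer that a faulty correction will be applied to the DR estimates. The documents do not support that, because no adjusted yield is specified anywhere. A reader might also divide the 12–15-month recruitment window by the 7–9-month implementation time and arrive at ratios up to 15/7 = 2.1. Those are different study-level periods, and nothing describes one FHC running for 15 months and another for 7. Nor should about 5.7 DR cases per FHC (8% of 1131/16) be taken as the expected yield, since every registered person with diabetes is to be invited and 1131 is only the required sample.

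What does not stand is the rescue by other sections. The prevalence denominator, the month-of-entry covariate and the time-series intention are not connected to this comparison. A gradient in counts may partly reflect coverage, but without a denominator it cannot be told apart from time open or register size.

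**Conclusion.** The point holds, with limited reach. The bias is misnamed, and the comparison as worded cannot adjust for incomplete ascertainment or for lead time. If screening time differs between FHCs, the artefact is about 1.29-fold at 9 v 7 months under constant throughput, and as little as 1.06-fold in the saturating case examined. If all FHCs are counted over one common window it disappears, and the timing statements do not settle whether they are. Using 9 v 7 months as a contrast between FHCs is itself an assumption, because the article gives that range for the study as a whole.

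A reader might infer that the main result is compromised. It is not: the proportion of the register screened and the figure of 1131 do not depend on this sentence. Only the interpretation of DR and STDR yield is affected.

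**What to change.** In the Sample size section:
1. Delete the claim to adjust for lead-time bias, rename the concern as incomplete ascertainment, and state that lead time cannot be estimated from a single cross-sectional round.
2. Replace the count comparison with DR and STDR per 100 people screened, by month since each FHC began screening. Set it beside the cumulative proportion of that FHC's register screened, using the start-of-study register already defined as the denominator. Label the whole as descriptive.

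The rate removes the dependence on screening time and register size, and the coverage column shows directly how much of the register remains unexamined. Neither corrects for early attenders differing from later ones or for the non-random order in which FHCs join, which is why the label should be descriptive. The cost is two sentences and a small extra tabulation of data already collected. The sample size and primary analysis do not change.

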### Statistical analyses

We will create a complete case data set of the cross-sectional survey for use in the analyses of effectiveness and assess the potential impact of missing data using sensitivity analysis incorporating a range of optimistic and pessimistic scenarios for the impact of missing data. We will model two outcomes that we hypothesised would be influenced by the intervention: (1) uptake of DR screening (primary outcome) and (2) numbers of patients referred for STDR as a result of screening. We will use bivariate logistic regression models to assess crude associations between sociodemographic factors such as age, gender, education, income and living arrangements, and other clinical data with DR and STDR and use fractional polynomials to account for the form of continuous covariates to predict uptake of DR screening. Factors associated with a p<0.25 will be candidates for inclusion in the multivariable logistic regression models. We will test interactions among identified main effects to capture improvement in model prediction assessed by reduced residual variance-based statistics. To account for the staggered entry into the study, we will add a variable indicating the month of entry of each FHCs into the programme (eg, 1. if the FHC join in the first month of the programme, 2. if in the second month and so on). A non-significant coefficient for this variable will suggest the staggered approach had no effect and a significant coefficient will allow the effect to be quantified for each FHC. In our final adjusted model, we will consider associations with a p<0.05 as statistically significant. Adequacy of model discrimination and calibration will be assessed using receiver operating characteristic curves. The validation of the telemedicine will be reported as the agreement (kappa statistics) between screen positive patients graded by the graders at the reading centre versus the DR grade as recorded by the ophthalmologists in secondary care centres. A kappa coefficient of 0.6 or higher was prespecified to indicate validity.

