**Methods and analysis:**

Currently, there is no systematic DR screening programme in Kerala. Our intervention is a teleophthalmology pathway for people with diabetes in the non-communicable disease registers in 16 family health centres. The planned implementation strategy of the pathway will be developed based on the discrete Expert Recommendations for Implementing Change taxonomy. We will use both quantitative data from a cross-sectional study and qualitative data obtained from structured interviews, surveys and group discussions with stakeholders to report the effectiveness of the DR care pathway and evaluation of the implementation strategy.

We will use logistic regression models to assess crude associations DR and sight-threatening diabetic retinopathy and fractional polynomials to account for the form of continuous covariates to predict uptake of DR screening. The primary effectiveness outcome is the proportion of patients in the non-communicable disease register with diabetes screened for DR over 12 months. Other outcomes include cost-effectiveness, safety, efficiency, patient satisfaction, timeliness and equity. The outcomes of evaluation of the implementation strategies include acceptability, feasibility, adoption, appropriateness, fidelity, penetration, costs and sustainability. Addition of more family health centres during the staggered initial phase of the programme will be considered as a sign of acceptability and feasibility. In the long term, the state-wide adoption of the DR care pathway will be considered as a successful outcome of the Nayanamritham study.

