### Description of the standard of care

Currently, patients with diabetes are not systematically screened for DR in the public health system. Most patients present to the tertiary centre voluntarily either because of increased awareness of complications of diabetes or due to visual impairment. Therefore, the current standard of care will be captured as the number of patients presenting to the tertiary centre for an eye consultation for DR over a period of time as there is no baseline data in the primary and secondary care. This cross-sectional survey of the patients presenting at the FHCs will provide information on the uptake of screening of people registered in the non-communicable diseases register at the start of the study. The prevalence of DR and STDR of the screened population will be estimated from the numbers screened in all the non-communicable diseases registers during this period.

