	Recruit, designate and train for leadership	A project manager will be recruited to manage the programme under the supervision of the non-communicable diseases lead. The Health Secretary will conduct periodic meetings with the project team to assess performance.
	Obtain formal commitments	A collaborative agreement is in place between Government of Kerala and Moorfields Eye Hospital, London, UK outlining their roles and responsibilities in the implementation of the DR care pathway.
	Prepare patients to be active participants	Community level health workers will prepare patients to be active in their care, to ask questions and specifically to inquire about care guidelines, the evidence behind clinical decisions or about available evidence-supported treatments. Each patient will provide written consent to be screened for DR in this project as well as participate in interviews after verbal consent.
	Inform local opinion leaders	The Health Minister of the Kerala state and members of the local government will be briefed on the project and encouraged to be champions of the project to enable scale up to all family health centres in the state.
Finance	Access new funding	Use GCRF/UKRI funding to purchase smartphone retinal cameras and retinal lasers, develop EHR, train staff at family health centres and secondary care, employ project manager, data entry operators and personnel to conduct interviews, create study database linked to hand-held applications for data entry operators. State and local government funds will be sourced for scale up.
	Incentivisation	ASHAs will be incentivised to accompany participants with diabetes who are referred to secondary care for treatment.
Education	Develop educational materials	Develop DR training modules and retinal image capture modules for family health centres staff Develop laser training material to train ophthalmologists.
	Distribute educational materials	Distribute educational materials (including guidelines, manuals and toolkits) in person, by mail and/or electronically. Multiple training sessions are planned at each family health centres. The camera manufacturers will be invited to provide hands-on training on capturing good quality retinal images. Training on laser surgery will also be provided to the ophthalmologists at secondary care.

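### The planned regression of screening uptake cannot be fitted to the data set named for it, although the crude uptake proportion can be counted

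*Protocol article*

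**What the plan says.** The abstract of the protocol article defines the primary outcome: "The primary effectiveness outcome is the proportion of patients in the non-communicable disease register with diabetes screened for DR over 12 months". The Sample size section fixes its denominator: "the denominator of numbers screened will be the number of people registered in the non-communicable diseases in each FHCs at the start". The start meant here is that of the survey. Tables 2 and 3 name the electronic health record (EHR), the study database and the register as sources for uptake.

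The Statistical analyses section then names the analysis set: "We will create a complete case data set of the cross-sectional survey for use in the analyses of effectiveness". The same paragraph lists uptake, labelled as the primary outcome, among the two outcomes to be modelled. Continuous predictors of uptake are to be handled with fractional polynomials, and receiver operating characteristic (ROC) curves are to be used to assess the models.

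Four other places show who is in that survey:
- Design: the study will "recruit consenting patients to a cross-sectional study to gather quantitative data for the effectiveness outcomes".
- Description of the standard of care: "This cross-sectional survey of the patients presenting at the FHCs will provide information on the uptake of screening of people registered".
- Table 1: "Each patient will provide written consent to be screened for DR in this project". Ethics and dissemination adds that all participants consent in writing before entry.
- Quantitative data: "Other study-specific data collected by nurses or data operators on the day of screening include education status, occupation and income categories". Body mass index, waist circumference and the lifestyle questionnaire belong to the same visit.

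On size, the Sample size section starts from a simple random sample of 377 out of 40 000 people with diabetes. For the design effect, "we assume it to be 3 to give a final sample size of 1131", which it equates to an intracluster correlation (ICC) of about 0.03 across 16 FHCs.

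**The concern.** A model of who takes up screening needs people who did and people who did not. The outcome is defined over everyone on the register, but the data set named for modelling it is built from people who came, consented to be screened and had their data taken on the screening day. The comparison group is excluded by the way the set is formed.

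At stake is the planned explanation of the primary outcome: which patients are reached, and how their characteristics relate to uptake. If the model were patched by comparing attenders with one another, it would answer a different question. Data on unscreened registrants must be arranged for in advance, and they cannot be recovered from the survey afterwards.

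The sample size has a related gap. It is said to rest on uptake, yet it describes a random sample that appears nowhere in the recruitment plan.

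**Working it through.** **1. Outcome and data set side by side.**
- Outcome: 1 if a registered person is screened, 0 if not, for everyone on the register at the start.
- Rows available: survey participants, who are present, consenting and consenting to be screened.
- Rows missing: registered people who did not attend or did not consent, which is where almost all the zeros lie.

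If every row has outcome 1, the logistic likelihood has no finite maximum: the intercept increases without limit and no slope is identified. Fractional polynomials have nothing to fit, and an ROC curve needs both outcome classes. Table 2 (Equity) does count people willing to be screened but denied it, so a few zeros are possible. Those people attended, so a model resting on them would describe denial of service and not uptake.

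**2. Do the missing-data scenarios help?** The optimistic and pessimistic scenarios concern missing values in the survey data set. A person who never entered the survey is not a row with a missing value, so the scenarios do not restore the non-attenders.

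**3. Which predictors exist for both groups?** Education, occupation, income, body mass index, waist and lifestyle are recorded on the screening day and so do not exist for non-attenders. Age, gender, diabetes duration and insulin use come from the EHR. They could exist for non-attenders, but the article does not say that they will be extracted for them.

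**4. The plan's sample size.** The expected proportion, precision and confidence level are not stated. Assuming p = 0.5, ±5 points and 95%:
- n0 = 1.96² × 0.25 / 0.05² = 384.1
- with N = 40 000: 384.1 / (1 + 383.1/40 000) = 380.5, so 381 against the stated 377, a difference of about 1%
- 377 × 3 = 1131, exact
- per FHC: 1131/16 = 70.7
- implied ICC: (3 − 1)/(70.7 − 1) = 0.029, in line with the stated 0.03

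The arithmetic is sound for a random sample of about 71 registered people per FHC. No such sample is drawn: the Target population section invites registered people, the Design section recruits those who consent, and uptake is counted over whole registers.

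**5. Precision over whole registers, as illustration only.** This assumes that 40 000 is the combined register of the 16 FHCs, which the article does not state. Mean register size is 40 000/16 = 2500. Design effect = 1 + 2499 × ICC, effective n = 40 000/design effect, and half-width at 50% uptake = 2.131 × √(0.25/effective n), using t with 15 degrees of freedom.

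| ICC | Design effect | Effective n | 95% half-width |
|---|---|---|---|
| 0.01 | 26 | 1539 | ±2.7 points |
| 0.03 | 76 | 527 | ±4.6 points |
| 0.10 | 251 | 159 | ±8.4 points |

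On the same assumption, if 1131 meant people screened, it would correspond to an uptake of 1131/40 000 = 2.8%. The unit therefore matters.

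**The case against.** The strongest reply is that the primary outcome is a count ratio from named sources. The denominator is fixed in the Sample size section, and Tables 2 and 3 point to the register, the EHR and the study database. This stands. A reader might infer that uptake cannot be estimated at all, and the documents do not support that: the proportion can be computed overall and for each FHC, and FHC-level counts could be modelled.

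Four further inferences also go too far:
- That 1131 is a number of screened patients. The text describes a random sample of people with diabetes. The fault is that this sample matches no recruitment step.
- That the plan commits to education and income as predictors of uptake. The sentence ties the sociodemographic factors to DR and sight-threatening DR, where models among screened people are feasible. For uptake it mentions only continuous covariates.
- That complete-case deletion will shrink the numerator of the crude proportion. Nothing says that the register proportion is computed after dropping screened people with incomplete covariates. The wording leaves it open, so it should be ruled out explicitly.
- That precision is inadequate. At the plan's ICC the illustrative ±4.6 points lies within the ±5 points that 377 appears to target. If these 16 registers are themselves the whole target, a full count has no sampling error.

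It can also be said that a journal article leaves extract details to the full protocol or analysis plan. That would excuse silence. Here the article names a specific data set for the effectiveness analyses, uptake model included, and that set does not contain the people the model needs.

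**Conclusion.** The point holds for the regression and not for the crude proportion. As written, uptake has essentially no variation in the data set assigned to it, so the uptake model and its ROC assessment cannot be produced at patient level, and no sensitivity analysis within the survey repairs this. The conclusion rests on reading the survey as consenting patients whose consent is to be screened, which four sections support. A few consenting but unscreened people would not change it.

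The sample-size point is secondary. The figures 377, 1131 and an ICC near 0.03 are mutually consistent, but 1131 has no defined role for a proportion counted over whole registers. The design effect of about 76 and the range of ±2.7 to ±8.4 points depend on the unstated assumption that 40 000 is the 16-FHC total, on equal register sizes and on an uptake of 50%. They illustrate scale and do not show that the study is too small.

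**What to change.** In Statistical analyses:
- Limit the complete-case survey set to the DR, sight-threatening DR and referral models.
- Take uptake from the baseline register list of people with diabetes, coded screened yes or no, and count every screened person whatever covariates are missing.
- Fit the uptake model on that list, using only fields that the register or EHR holds for attenders and non-attenders: for example age, gender, diabetes duration and insulin use where held, FHC and its month of entry.
- If an individual extract is not possible, model screened and registered counts by FHC. With 16 units this supports very few predictors.

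In Sample size: say what unit 1131 counts and which analysis it serves, say whether 40 000 is the combined register of the 16 FHCs, and restate the precision of the register proportion on the basis of 16 FHCs.

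The cost is wording plus one anonymised register extract. The article already plans to analyse anonymised EHR extracts, but the sponsor should confirm that the approval covers registered people who have not consented. The uptake model loses the socioeconomic and lifestyle predictors, which could not have predicted uptake in any case because they exist only for attenders.
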